### **Tumor Incidence**

The occurrence of any tumor will be recorded on the AE-CRF. Additionally they will be subject to expedited reporting according to the SAE-criteria described below.

### **Adverse events**

An adverse event is the appearance or worsening of any undesirable sign, symptom, or medical condition occurring after obtaining informed consent even if the event is not considered to be related to study drug. Study drug includes the investigational drug under evaluation and the comparator drug or placebo that is given during any phase of the trial. Medical conditions/diseases present before starting study drug are only considered adverse events if they worsen after starting study drug. Abnormal laboratory values or test results constitute adverse events only if they induce clinical signs or symptoms, are considered clinically significant, or require therapy.

The occurrence of adverse events should be sought by non-directive questioning of the patient at each visit during the study. Adverse events also may be detected when they are volunteered by the patient during or between visits or through physical examination, laboratory test, or other assessments. As far as possible, each adverse event should be evaluated to determine:

1. the severity grade (mild, moderate, severe)
2. its relationship to the study drug (Certican®, Simulect® dose 3 & 4)  
(suspected/not suspected)
3. its duration (start and end dates or if continuing at final exam)
4. action taken i.e:
  - (a) no action taken;
  - (b) study drug dosage adjusted/temporarily interrupted;
  - (c) study drug permanently discontinued due to this adverse event;
  - (d) concomitant medication taken;
  - (e) non-drug therapy given;
  - (f) hospitalization/prolonged hospitalization)
5. whether it is serious, where a serious adverse event (SAE) is defined as one which:
  - is fatal or life-threatening
  - results in persistent or significant disability/incapacity
  - constitutes a congenital anomaly/birth defect
  - requires inpatient hospitalization or prolongation of existing hospitalization, unless hospitalization is for:
    - routine treatment or monitoring of the studied indication, not associated with any deterioration in condition

- elective or pre-planned treatment for a pre-existing condition that is unrelated to the indication under study and has not worsened since the start of study drug
- treatment on an emergency outpatient basis for an event not fulfilling any of the definitions of a SAE given above and not resulting in hospital admission
- social reasons and respite care in the absence of any deterioration in the patient's general condition
- is medically significant, i.e., defined as an event that jeopardizes the patient or may require medical or surgical intervention to prevent one of the outcomes listed above
- is a graft loss
- is the occurrence of any neoplasm or tumor

**Unlike routine safety assessments, SAEs are monitored continuously and have special reporting requirements; see Section 8.1.**

All adverse events should be treated appropriately. Such treatment may include changes in study drug treatment including possible interruption or discontinuation, starting or stopping concomitant treatments, changes in the frequency or nature of assessments, hospitalization, or any other medically required intervention. Once an adverse event is detected, it should be followed until its resolution, and assessment should be made at each visit (or more frequently, if necessary) of any changes in severity, the suspected relationship to the study drug, the interventions required to treat it, and the outcome.

Information about common side effects already known about the investigational drug can be found in the Investigator Brochure or will be communicated between IB updates in the form of Investigator Notifications. This information will be included in the patient informed consent and should be discussed with the patient during the study as needed.

### **Physical examination**

Information about the physical examination must be present in the source documentation at the study site. Significant findings that are present prior to study enrollment must be included in the Relevant Medical History/Current Medical Conditions CRF. Significant findings made after the start of the study which meet the definition of an AE must be recorded on the AE CRF.

### **Vital signs**

Height will be recorded at Baseline visit 1 (Visit 1) only. Vital signs will be recorded at every study visit, and include oral body temperature, radial pulse rate, systolic and diastolic blood pressure and weight (kg). Blood pressure and pulse rate will be assessed after the patient has rested in the sitting position for at least five minutes; blood pressure should be assessed at the same arm each time of determination.

### **Laboratory evaluations**

The center's local laboratory will be used to analyze the clinical laboratory data during the study.

The following variables will be examined:

Hematology: Hemoglobin, leukocytes (differential blood count), absolute neutrophil count and platelet count, hematokrit (HK)

Blood chemistry: creatinine, urea, sodium, potassium, calcium, ALAT, ASAT, protein, AP, albumin, C-reactive protein (CRP), phosphate, magnesium, CPK

Additionally at Baseline Visit 1 (= extended program):  
total cholesterol, LDL, HDL, triglycerides,

Additionally at Baseline Visit 2 and Month 6  
(= complete program):

glucose (fasting), ferritin, transferrin, serum iron  
total cholesterol, LDL, HDL, triglycerides,

Viral Serology: Hepatitis B (HBsAg), Hepatitis C, HIV (only at Baseline visit 1), CMV

Urinalysis: creatinine, protein, albumin

For determination of the drug levels see [Section 7.9](#).

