**Exclusion Criteria**

1. Multi-organ recipients (e.g., kidney and pancreas)
2. Patients receiving a kidney from a non-heart beating donor
3. Patients who are recipients of A-B-O incompatible transplants
4. Patients with a historical (or current) peak PRA of > 25% (current = 3 months)
5. Patients with already existing antibodies against the HLA-type of the receiving transplant
6. Patients with any known hypersensitivity to Simulect®, Certican®, mycophenolic acid, cyclosporine A, other drugs similar to Certican® (e.g., macrolides), or other components of the formulations (e.g. lactose)
7. Patients who have received an investigational immunosuppressive drug within four weeks prior to study entry (Baseline visit 1)
8. Patients with thrombocytopenia (platelets < 75,000/mm^3), with an absolute neutrophil count of < 1,500/mm^3 or leucopenia (leucocytes < 2,500/mm^3), or hemoglobin < 6 g/dL
9. Patients with symptoms of significant somatic or mental illness. Inability to cooperate or communicate with the investigator, who are unlikely to comply with the study requirements, or who are unable to give informed consent
10. Patients who are HIV, HCV RNA, or Hepatitis B surface antigen positive
11. Evidence of severe liver disease (incl. abnormal liver enzyme profile, i.e. AST, ALT or total bilirubin > 3 times UNL)
12. Females at randomization who will be not considered post-menopausal according to the following definition:  
= 12 months of natural (spontaneous) amenorrhea or  
= 12 month post surgical bilateral oophorectomy or  
hysterectomized women over or equal to 65 years of age
13. Presence of a clinically significant infection requiring continued therapy, severe diarrhea, active peptic ulcer disease, or uncontrolled diabetes mellitus that in the opinion of the investigator would interfere with the appropriate conduct of the study
14. History of malignancy of any organ system, treated or untreated, within the past 5 years whether or not there is evidence of local recurrence or metastases, with the exception of localized basal cell carcinoma of the skin
15. Evidence of drug or alcohol abuse

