#### **Exclusion Criteria**

The following exclusion criteria must not be present at Baseline visit 1 (BL1, Screening visit prior to transplantation)

1. Multi-organ recipients (e.g., kidney and pancreas)
2. Patients receiving a kidney from a non-heart beating donor
3. Patients who are recipients of A-B-0 incompatible transplants
4. Patients with a historical or current peak PRA of > 25% (current = 3 months)
5. Patients with already existing antibodies against the HLA-type of the receiving transplant
6. Patients with any known hypersensitivity to Simulect®, Certican®, mycophenolic acid, cyclosporine A, other drugs similar to Certican® (e.g., macrolides), or other components of the formulations (e.g. lactose)
7. Patients who have received an investigational immunosuppressive drug within four weeks prior to study entry (Baseline visit 1)
8. Patients with thrombocytopenia (platelets < 75,000/mm^3), with an absolute neutrophil count of < 1,500/mm^3 or leucopenia (leucocytes < 2,500/mm^3), or hemoglobin < 6 g/dL
9. Patients with symptoms of significant somatic or mental illness. Inability to cooperate or communicate with the investigator, who are unlikely to comply with the study requirements, or who are unable to give informed consent
10. Patients who are HIV, HCV RNA, or Hepatitis B surface antigen positive
11. Evidence of severe liver disease (incl. abnormal liver enzyme profile, i.e. AST, ALT or total bilirubin > 3 times UNL)
12. Females at randomization who will be not considered post-menopausal according to the following definition:
  - = 12 months of natural (spontaneous) amenorrhea or
  - = 12 month post surgical bilateral oophorectomy or
  - hysterectomized women over or equal to 65 years of age
13. Presence of a clinically significant infection requiring continued therapy, severe diarrhea, active peptic ulcer disease, or uncontrolled diabetes mellitus that in the opinion of the investigator would interfere with the appropriate conduct of the study
14. History of malignancy of any organ system, treated or untreated, within the past 5 years whether or not there is evidence of local recurrence or metastases, with the exception of localized basal cell carcinoma of the skin
15. Evidence of drug or alcohol abuse

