#### **Exclusion Criteria**

Of all patients included into the study at BL1 (prior to transplantation), those can not continue into the randomized study period, in whom one of the following criteria are met at BL2, prior to randomization:

1. Graft loss after current transplantation (since Baseline visit 1)
2. Patients who received a depleting antibody therapy or more than 10mg/day prednisolon (or an equivalent oral steroid therapy)
3. Patients who suffered from rejection (more than BANFF 1A), recurrent acute rejection, or steroid resistant acute rejection
4. Patients with thrombocytopenia (platelets < 75,000/mm^3), with an absolute neutrophil count of < 1,500/mm^3 or leucopenia (leucocytes < 2,500/mm^3), or hemoglobin < 6 g/dL
5. Evidence of severe liver disease (incl. abnormal liver enzyme profile, i.e. AST, ALT or total bilirubin > 3 times ULN)
6. Current dialysis dependency at Baseline visit 2
7. Patients with clinically significant infection requiring continued therapy which would interfere with the objectives of the study
8. Presence of intractable immunosuppressant complications or side effects (e.g., severe gastrointestinal adverse events) at randomization visit (Baseline visit 2)

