3. Demographic data will be recorded (sex, age, ethnic origin)

4. Relevant medical history will be obtained and recorded (diabetes mellitus); the smoking status will be recorded and the cardiovascular risk (Framingham Score, see [Appendix 7](#)) will be calculated.
5. Transplantation information will be recorded (donor and recipient information).
6. A complete physical examination will be performed.
7. Vital signs will be measured.
8. Venous blood will be drawn for measurement of hematology and biochemistry (extended program)
9. Venous blood will be drawn for measurement of viral serology
10. Concomitant medications / significant non-drug therapies will be recorded.
11. Optionally –if part of center standard procedure- a control biopsy may be taken after transplantation. Control biopsies should be assessed by a central nephropathologist. In order to avoid any bias, which could interfere with the objectives of the study, investigators should be kept blinded until completion of the study.

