## **Laboratory data**

Abnormalities according notable criteria (see [Appendix 2](#)) will be identified. The proportions of patients with clinically notable abnormalities according to the notable criteria will be summarized. Shifts from baseline value to worst post-baseline value based on the normal ranges will be presented graphically ([Amit et al., 2008](#)). The worst observation is defined as the highest or lowest measure during the different observations periods whereby high or low are chosen according to the direction of abnormality. Further, descriptive statistics of change from baseline of all laboratory variables will be presented by visit. A by-patient listing of all clinically notable abnormal laboratory data will be generated. Only assessments obtained up to 7 days after the discontinuation of study medication will be considered “on-treatment” and analyzed with relationship to immunosuppressive therapy.

The relative frequency of proteinurea will be tabulated by treatment group and visit.

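### Total bilirubin is a limit in the liver exclusion at both baselines and has a notable-value criterion, but no laboratory program in Section 7.6 schedules it

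*Protocol*

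**What the plan says.** **Eligibility.** Exclusion 11 at BL1 (Synopsis and Section 5) covers severe liver disease and names as laboratory limits "AST, ALT or total bilirubin > 3 times UNL". Exclusion 5 at BL2, checked before randomization, repeats it: "Evidence of severe liver disease (incl. abnormal liver enzyme profile, i.e. AST, ALT or total bilirubin > 3 times ULN".

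**Safety reporting.** Appendix 2 lists bilirubin among the liver variables, with a notable value of at least 3 x ULN, alongside AST and ALT at the same multiple. Section 10.5.2 (Laboratory data) puts these criteria to use: "The proportions of patients with clinically notable abnormalities according to the notable criteria will be summarized".

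**Measurement.** Section 7.6 (Laboratory evaluations) gives the panel common to all programs: "Blood chemistry: creatinine, urea, sodium, potassium, calcium, ALAT, ASAT, protein, AP, albumin, C-reactive protein (CRP), phosphate, magnesium, CPK". The extended program adds total cholesterol, LDL, HDL and triglycerides. The complete program adds "glucose (fasting), ferritin, transferrin, serum iron" and the same lipids.

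**The concern.** One section sets a limit on an analyte, another plans to tabulate it, and the section that says what is measured leaves it out. Two things are at stake.

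The first is eligibility. A site that carries out exactly the scheduled tests has AST and ALT at both baselines but no bilirubin. A patient above the bilirubin limit with AST and ALT below theirs would not be picked out by any protocol-specified test, either before transplantation or before randomization.

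The second is safety reporting. Section 10 rests the safety assessment mainly on adverse events and on laboratory values outside set ranges. One of those ranges would have no scheduled values behind it, so whether a transaminase rise came with a bilirubin rise could not be examined systematically.

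**Working it through.** No arithmetic beyond counting applies, and the plan gives no figure to reproduce. The check sets the places that use bilirubin against those that schedule tests.

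**Where bilirubin is named**

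| Place | Use |
|---|---|
| Synopsis, BL1 exclusion 11 | limit > 3 x ULN |
| Section 5, BL1 exclusion 11 | limit > 3 x ULN |
| Synopsis, BL2 exclusion 5 | limit > 3 x ULN |
| Section 5, BL2 exclusion 5 | limit > 3 x ULN |
| Appendix 2 | notable value ≥ 3 x ULN |

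**What is drawn at each visit** (Table 7-1 and visit descriptions, with the content from Section 7.6)

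| Visit | Week | Program | AST, ALT | Bilirubin |
|---|---|---|---|---|
| 1 (BL1) | 0 | extended | yes | no |
| 2 | 2 | basic | yes | no |
| 3 (BL2) | 7 | complete | yes | no |
| 4 | 8 | everolimus level only | no | no |
| 5 | 12 | basic | yes | no |
| 6 | 18 | extended | yes | no |
| 7 | 24 | complete | yes | no |

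The other scheduled tests (viral serology, urinalysis and GFR, glucose tolerance test with insulin, drug levels, optional biomarkers) do not include bilirubin either.

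**Counts**

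- Bilirubin is named in four exclusion statements (two baselines x two places) and one criteria table, and in none of the three laboratory programs.
- Of the three laboratory limits in the liver exclusion, two (AST, ALT) have a scheduled test at both baselines and one (total bilirubin) has none: 3 − 2 = 1.
- Of the six scheduled chemistry draws (Weeks 0, 2, 7, 12, 18 and 24), none includes bilirubin.

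**Who is affected in the safety table.** Section 10.5.2 analyzes safety variables in the safety set. Section 10.1 defines that set as transplanted patients with at least one dose of immunosuppression after BL1, so it includes patients who were never randomized. Its expected size is not stated.

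**A parallel case.** Uric acid also has thresholds in Appendix 2 and appears in none of the three programs. It is not an eligibility limit, so there the mismatch touches only the notable-value table.

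**The case against.** The case on the other side has four parts, and much of it stands.

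- **The list in Section 7.6 is not shown to be closed.** It says what will be examined, not that nothing else may be. BK virus in serum and the glucose tolerance test with insulin are required elsewhere and are missing from that list. This stands: omission from the list does not forbid the test.
- **Eligibility is a separate step from the laboratory programs.** ABO compatibility and pre-existing HLA antibodies also have no scheduled test and must come from the record. Local laboratories are used, and Section 9.1 requires full verification of adherence to the entry criteria against source documents. A site may well hold a routine bilirubin value. A reader might infer that the liver exclusion cannot be applied at all; the documents do not support that. The criterion is met by any one of the three limits, or by other evidence of severe liver disease. What remains is narrower: the protocol neither requires nor refers to a routine value for this limit, so its availability is left to each center.
- **Liver safety is still monitored.** A reader might infer that the report would show no liver signal because the test was not done. That goes too far. AST, ALT and AP are in every chemistry draw, AST and ALT have notable criteria, and clinically significant laboratory abnormalities are adverse events under Section 7.6. What is lost is scheduled bilirubin and its joint reading with the transaminases.
- **Appendix 2 sets thresholds and does not prescribe tests.** True, and some of its rows carry no threshold at all. But Section 10.5.2 plans to summarize the criteria, and a row that can only be filled from unscheduled values is incomplete in a way that may differ between centers.

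A reader might also size the gap as the 244 planned randomized patients. The relevant denominator is the safety set, which is defined differently.

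**Conclusion.** The point holds as a conflict between sections. Section 7.6 schedules no total bilirubin, while both baseline exclusions and Appendix 2 rely on it. Protocol-specified tests leave one of three laboratory limits unconfirmed at BL1 and at BL2, and the notable-bilirubin row has no scheduled measurements at any of the six chemistry draws.

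How many ineligible patients might pass for this reason cannot be estimated from the protocol. Such a patient would need a raised bilirubin, AST and ALT below the limit, no other evidence of severe liver disease, and no routine bilirubin value on file. How often sites hold such a value is not stated and is not assumed here.

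The effect is confined to eligibility checking and safety tabulation. The primary GFR analysis, the randomization and the sample size are untouched. The correction should be made because it makes a stated safety limit verifiable at almost no cost.

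**What to change.** Reconcile Section 7.6 with BL1 exclusion 11, BL2 exclusion 5 (in the Synopsis and in Section 5) and Appendix 2 by adding total bilirubin to the common blood chemistry list. Because that list is part of all three programs, one addition covers BL1, Week 2, BL2 and Weeks 12, 18 and 24, with no new visit or blood draw. The BL1 and BL2 results should be available when eligibility is checked.

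The cost is one further analyte at the local laboratory and one CRF field.

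As housekeeping, either add uric acid to the same list or delete its row from Appendix 2.

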### **Viral serology**

All patients will be tested for Hepatitis B (HBsAg), Hepatitis C, CMV and HIV at Baseline visit 1, earlier tests  $\leq 6$  months are acceptable. Any patients with a positive Hepatitis B surface antigen or Hepatitis C or HIV will be excluded. If results are not available at Baseline visit 1, the patient may be included. If results of a newly initiated assessment at Baseline visit 1 or thereafter will be positive, the patient will subsequently be dropped from the study and administered the standard care provided by the center.

Any patients with a negative CMV status should be tested at Baseline visit 1 and Baseline visit 2 for CMV. Furthermore BK virus will be assessed in serum at Baseline visit 2 and at the end of the study.

### **New-Onset of Diabetes Mellitus**

At Baseline visit 2 and on week 24 (EOS) assessments will be performed to investigate the development of a diabetes mellitus. Therefore, fasting blood sugar level will be analyzed as well as an oral glucose tolerance test with a concomitant insulin measurement will be performed.

### **Cardiovascular Risk (Framingham Score)**

At BL1 (Screening), BL2 (Week 7), Final Assessment (Month 6) as well as at the yearly follow-up assessments the patients' cardiovascular risk will be calculated using the Framingham score.

This update of the 1991 Framingham coronary prediction algorithm as used in this study ([Wilson et al., 1998](#)) provides estimates of total risk of developing one of the following coronary heart diseases: angina pectoris, myocardial infarction, or coronary disease death, over the course of 10 years. The factors used to estimate risk include age, LDL cholesterol, HDL cholesterol, blood pressure, cigarette smoking, and diabetes mellitus. Different score sheets are used for men and women ( [Appendix 7](#)).

## **7.7 Tolerability**

No specific tolerability measure is used in this study. However, tolerability of study medication can be assessed from the rate of patients who withdraw prematurely from study medication or in whom study medication had to be converted to another immunosuppressive regimen due to abnormal laboratory results, adverse events, or toxicity.

All changes to the immunosuppressive medication dosing regimen will be recorded on the Dosage Administration Record CRF, along with the reason for change.

## **7.8 Health-related Quality of Life**

None.

## **7.9 Pharmacokinetics**

The actual sample collection times, and the date and time of the previous drug dose (Certican® or Sandimmun® Optoral) will be recorded on CRF using a 24 hour clock.

Cyclosporine whole blood levels will be measured starting at Visit 2. For patients of the Control group cyclosporine blood level will be measured at every study visit, for patients of the CNI-free Certican group cyclosporine blood level will be measured until Sandimmun® Optoral is removed from the immunosuppressive regimen (Visit 3, Week 7).

Certican® (everolimus) blood levels will be measured in patients of the Certican® group starting 7 days after first Certican® dose application, and at every study visit thereafter.

- **Cyclosporine (CsA) whole blood tests**

Analysis of the cyclosporine whole blood levels will be performed locally at the center. Whole blood level for CsA will be assessed by utilizing a monoclonal immunoassay or HPLC-method on blood taken 5 minutes prior to medication intake (C0-h level), as indicated in the visit schedule (C-0h).

- **Certican® (everolimus) whole blood tests**

For the analysis of the everolimus whole blood levels 2 ml of blood should be drawn in EDTA tubes. Analysis will be performed using ELISA method. The C-0h level will be obtained with blood sampling within 5 minutes prior to medication intake.

